### 2.4. Randomization

After signing the written informed consent, eligible participants will be randomly assigned to the active control group, and one of the three experimental intervention groups by the principal researchers. The randomization procedure will be run by an independent statistician using a computerized randomization program. The participants do not know the real purpose of the study, they are just told that they are participating in a project that aims to enrich the life of community dwelling older adults and that they are randomly allocated to different groups of the project according to a computerized randomization program. Participants and two principal researchers know the group assignments. Those who perform the intervention and outcome measures will be blinded to the allocation of participants.

### 2.5. Interventions and Control Condition

Participants in each intervention group will be told to enroll in a 24-week program and complete 50 min sessions three times a week, and to keep their regular daily life in normal living condition. All interventions will be conducted in the community center under the supervision of personnel who will be trained by the principle researchers to ensure the standardized administration of the intervention protocols.

The intervention conditions include: (1) open-skill exercise condition, which involves a combination of physical and cognitive training, (2) closed-skill exercise condition, which involves physical exercise training alone, (3) mobile game playing condition, which is considered as cognitive training alone, (4) active control condition.

#### 2.5.1. Open-Skill Exercise Condition

The open-skill exercise group will participate in a specially designed table tennis training program. The exercise intervention will be performed in a sequence of increasing complexity under the instruction of trainers. The trainers will be chosen from college students majoring in table tennis training.

The procedure of each single intervention session includes a warm-up, training in the basic skills of table tennis, playing table tennis with each other, special tasks designed to increase the cognitive load, and a cool down period. The aim of basic skills training is to improve general skills. It includes the following component: serving, backhand blocking, forehand attacking, left side blocking, and right side attacking (including footwork). After the coaches have demonstrated the basic skills, participants will practice with each other (or with the coaches). Training for each skill begins with simple movement, and then progresses to more complex skills, according to their degree of mastery.

To add more cognitive load to physical exercises during the process of learning the basic skills, tasks must be planned and a program of movement will be designed. This approach will be structured to achieve a particular type of training that is expected to relate to executive function. Table-tennis balls will be successively thrown to participant by a serving machine on one side of the ping-pong table. Participants stand on the other side of the table, and must anticipant the ball trajectory to intercept it. Balls are of two different colors; half are white and half are yellow. Three different tasks were designed to increase cognitive load. Participants must intercept the white ball but ignore the yellow ball in task 1, which requires inhibition function during movement. Task 2 requires participants to hit the white ball to the left side and the yellow ball to the right side across the ping-pong table. which needs task-switch ability. Task 3 was designed to train the working memory ability by asking participants to hit the ball to the left side if the previous ball is white and to the right if previous ball is yellow.

All participants will be required to move continuously during the training to maintain an average individual target heart rate reserve (HRR) of 40–59%.

#### 2.5.2. Closed-Skill Exercise Condition

The closed-skill exercise group will use a cycle ergometer or motor-driven treadmill with a moderate intensity (40–59% HRR). Each training session will include a warm-up, cycle ergometer riding or brisk walking/jogging for 30 min, and cool down period. Intensity and duration will be progressive during the training period. The Borg Rating of Perceived Exertion (RPE) will be used every 5 min during exercise to monitor the subjective feeling of exertion.

#### 2.5.3. Mobile Game Playing Condition

The cognitive training group will play a table tennis mobile game on the mobile phone without body movement. The mobile game is called Table Tennis Touch, and is a free sport action mobile multiplayer game featuring stunning graphics, intuitive swipe controls, high speed gameplay and multiple game modes developed by the British Indie Studio Yakuto. It offers a fantastic simulation of real table tennis playing settings. Players can serve, spin, and smash their way to winning. The older adults will be trained the first time, and will subsequently play under the supervision of the trainers.

#### 2.5.4. Active Control Condition

To control for the Hawthorne effect, which means participants may change their behavior just by being aware that they are being watched, the control group will also do some stretching and toning of the same duration and frequency as the intervention group. Social engagement will be similar among all groups.

### 2.6. Outcome Measures

Demographic variables will be collected during the evaluation, and include age, gender, weight, height, mental status, visual acuity, resting heart rate and blood pressure. The outcomes include objective and subjective measurements of cognitive and physical activities. All outcomes will be measured prior and immediately after the intervention, and at 3 months after the intervention. After 12 weeks, there will be an intermediate measurement, consisting of the primary outcome measures.

#### 2.6.1. Primary Outcome

The primary outcome measure of this study is objective visuospatial working memory. It is measured by the visuospatial working memory task (VWMT) developed by Guo et al., (2016), which includes both the passive storage and active manipulation of visuospatial information [32]. Participants will be asked to hold a 4 × 4 matrix with four solid black squares as a probe stimulus in memory for 3 s, and mentally rotate the matrix 90° to the right or the left at the same time. The task is used to decide whether the testing stimulus is consistent with the mentally rotated probe stimulus 90° either to the left or right.

Passive storage and active manipulation will be measured separately to reveal the mechanism driving differences on visuospatial working memory. The passive storage of visuospatial information will be tested by visuospatial short-term memory task (VSMT). The experimental paradigm of VSMT is similar to that of VWMT, except that subjects are instructed to retain the memory stimulus during the retention interval. Participants must determine whether the testing stimulus is identical to the memory stimulus. Active manipulation of visuospatial information will be tested by the visuospatial mental rotation task (VMTT). A pair of matrices will be presented on the screen for 6 sec. Participants must compare the two matrices to determine whether the one on the right side corresponds to a 90° rotation of the one on the left side.

#### 2.6.2. Secondary Outcomes

The subjective memory complaint (SMC) occurs long before the decline of working memory during aging [35]. It will also be measured in this study. SMC will be rated using the Memory Complaint Questionnaire (MAC-Q). The six-item MAC-Q requires participants to compare current memory function to memory function at earlier ages in daily scenarios. For each question, there are five possible answers, ranging from “much better now” (scored 5) to “much worse now” (scored 1). Serious SMC is defined as a total score below 15 [36]. MAC-Q demonstrates good internal consistency together with satisfactory test-retest reliability [37].

The attention network test (ANT) will be used to assess the alerting, orienting, and executive networks of the attentional system independently in a single test [38]. The test is a combination of the Flanker paradigm and a cueing task, with four cue types (no, central, double, and spatial) and three flanker types (congruent, incongruent, and neutral). The cue stimuli are asterisks, and are always valid to provide temporal information about the coming target stimuli. The target stimuli are five horizontal arrows that serve as flankers. Participants will be instructed to respond to the central arrow as fast and as accurately as possible [39,40].

A matrix reasoning test (MRT) will be used to measures abstract nonverbal reasoning ability. This test includes 35 items, in which the individual is required to look at an incomplete matrix and select the missing portion from five response options. This test is a subtest of the Wechsler Abbreviated Scale of Intelligence, and is relatively language free [41]. The score is generated based on the number of items completed correctly.

The Taiwan version of the International Physical Activity Questionnaire (IPAQ) will be used as a subjective measurement to estimate the total amount of physical activity in the preceding week.

The Mi Band wristband will be used to measure objective physical activity. Participants will be asked to wear the wristband all day from one week before the intervention, during the whole intervention, during the 3-month post-intervention. The wristband inserts a 3-axis acceleration sensor ADXL362 that measures the number of walking steps and distance travelled in everyday life. The wristband will also monitor the heart rate during intervention.

## 3. Discussion

Previous studies that evaluated how open/closed-skill exercises affected the cognitive functions of older people mainly used a cross-sectional design [25,32]. There has been only one longitudinal study using a 6-month randomized controlled trial [27]. The longitudinal study showed that older adults who participated in open-skill exercises had better executive function compared to those that participated in closed-skill exercises. However, the mechanism underlying the additional advantage of open-skill exercises remains subject to debate. One major strength of the proposed study protocol is its design with four groups. In addition to the open-skill, closed-skill, and control group, there will be a cognitive training group. The inclusion of a cognitive training group provides the opportunity to separate the physical activity component and cognitive activity component by comparing differences among the groups. This approach might reveal the possible mechanisms driving the additional cognitive benefits of open-skill exercises. The closed-skill group and cognitive training group will only have the physical activity and cognitive activity component, respectively, while the open-skill exercise group will involve both physical and cognitive components. The cognitive training group will use a table tennis mobile game that differs previous computerized cognitive training [42,43], as it will utilize the same cognitive component as the open-skill exercise group.

Several studies have explored various methods to combine cognitive and physical training as a tentative approach to improve cognitive functions. On one hand, according to the cardiovascular fitness hypothesis, participant in chronic exercises may lead to changes in cardiovascular system, this change can increase cerebral blood flow and the up-regulation of neurotransmitters [44]. On the other hand, cognitive training can guide and integrate new neurons and synapses into existing neural networks [45]. Therefore, the combination of the two interventions may induce superimposed cognitive benefits. The combination of cognitive and physical training typically being completed separately or simultaneously. It has been demonstrated that simultaneous combination has a larger effect on cognitive function compared to their being conducted separately. The simultaneous combination is usually conducted as dual-tasks, such as pedaling on a stationary bike while learning the memory strategies and practicing the memory drills presented by a trainer on the screen in front of them [46]. These combinations are not popular by the elderly population due to the difficulty of implementation. Thus, open-skill exercises that are played in a dynamically changing, unpredictable, and external environment, and require a cognitive component, represent better choice. Similar to table tennis used in this proposed study, Moreau et al., (2015) designed training that was loosely based on freestyle wrestling. This approach favored new motor coordination via demonstrations and active trial-and-error problem-solving with a partner. After 8 weeks training, the designed sport group showed the largest gains in all cognitive measures. [47]. Open-skill exercises can be viewed as high ecologically validated approaches that combine cognitive and physical training simultaneously.

This proposed project differs to previous studies by measuring visuospatial working memory as a primary outcome, rather than general cognitive function. This is key because visuospatial working memory ability declines more severely after the age of 60. Additionally, a previous cross-sectional study of older adults only revealed a possible relationship between exercise mode and visuospatial working memory. In comparison, the proposed longitudinal project will explore the reasons why open-skill exercises generate more benefits on visuospatial working memory. The subjective memory complaint (SMC) will also be measured alongside the objective measures of working memory. SMC is defined as the reporting of memory problems without pathological results on neuropsychological tests. SMC is associated with later cognitive decline and a higher incidence of dementia [48]. A randomized controlled study reported that 12 weeks of exercise interventions induced beneficial effects on memory complaints (tested by MAC-Q), but not on objective memory performance (tested by the Prose Test and Rey test) [49]. In addition to SMC, the proposed study will investigate the association between MAC and visuospatial working memory, which have been subject to controversy in previous studies.

A limitation of the study is that outcome measures mainly include cognitive domains. However, the general aim of exercise is to provide benefits on the overall aspects of well-being, including both cognitive functions and physical performance. Apart from the included measures of physical activities, other measures of cardiovascular fitness and physical performance such as mobility, balance, strength and endurance will also be added to evaluate the physical functions in future studies.

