Cognitive function reacts sensitively to environmental changes, and can be significantly improved after certain intervention. Several studies have shown that cognitive function may benefit from physical exercise in older adults [5,6,7]. Yet, Diamond et al., (2016) argued that aerobic exercise without any cognitive component produces little or no cognitive benefit. The authors predicted that, besides direct exercise training, successful approaches should incorporate cognitive, emotional, and social needs [8]. The authors also stressed that certain modes of physical exercise, including aerobic-exercise and resistance-training, are among the least effective ways of improving executive functions [9]. Therefore, physical training should extend beyond simple moving to moving with thought [10]. Fortunately, various studies have started to focus on identifying cognitive benefit from combinations of cognitive training and physical exercise. Some studies examined these components separately, while others conducted the two components simultaneously. The separate approach usually involves cognitive trainings (e.g., focus on memory, attention, executive function, visuospatial ability), followed by physical exercise (e.g., aerobic exercise, resistance training), or vice versa [11,12,13,14,15,16]. The simultaneous approach is usually conducted in dual-tasks, such as completing the cognitive task during physical exercise [17,18,19,20] or in exergames, which combine physical exercise with computer-simulated environments and interactive videogame features [7,21]. In general, that simultaneous approach tends to have a larger effect size than the separate approach on cognition [22,23]. However, concerns exist that the similarity between cognitive assessments and dual-tasks produce a learning effect that impacts the reliability of the results. Laboratory based intervention cannot easily be generalized to everyday life of the elderly.

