## 4. Conclusions

The overall goal of this study is to compare the effects of open-skill exercises on cognition in older adults. If successful, the results of the proposed study provide important evidence-based recommendations for older adults to select the most efficient and effective exercise mode to improve cognitive function. In particular, this study will reveal the mechanism driving the additional cognitive benefits of open-skill exercises compared to closed-skill exercises.

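### The phone game is said to share the open-skill arm's cognitive component, but only the open-skill arm is given three executive drills, so the mechanism claim is not supported

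*Protocol article*

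**What the plan says.** The Discussion presents the four-group design as a major strength because including a cognitive training group "provides the opportunity to separate the physical activity component and cognitive activity component by comparing differences among the groups". The ground given is that the phone game differs from earlier computerised training in that "it will utilize the same cognitive component as the open-skill exercise group". The Introduction and section 2.5 use the same decomposition: open-skill exercise is physical plus cognitive, closed-skill is physical alone, and the game is cognitive alone. The Conclusions then state that "this study will reveal the mechanism driving the additional cognitive benefits of open-skill exercises compared to closed-skill exercises".

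Section 2.5.1 describes an open-skill programme that goes beyond learning and playing table tennis. Each session also contains special tasks with two-coloured balls from a serving machine: "Three different tasks were designed to increase cognitive load". They are meant to provide "a particular type of training that is expected to relate to executive function". In the first, participants must "intercept the white ball but ignore the yellow ball in task 1, which requires inhibition function during movement". The second sends each colour to a different side and is said to need task switching. The third makes the response depend on the colour of the previous ball: "Task 3 was designed to train the working memory ability".

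Section 2.5.3 describes the game arm as supervised play of an existing table tennis phone game without body movement, with serving, spinning and smashing. It describes no inhibition, switching or previous-stimulus task. Section 2.6.1 makes visuospatial working memory the primary outcome.

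**The concern.** Subtracting one arm from another isolates a component only if the two arms are alike in everything else. The plan asserts this for the cognitive content of the game and open-skill arms, but its own description of the interventions contradicts it. One arm alone receives tasks built to train executive function, and one of those tasks targets working memory.

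A better result in the open-skill arm could then come from the drills, from open-skill play, from the physical activity, or from a mixture. Read as the plan proposes, an advantage over the game would be credited to physical activity. An advantage over cycling or treadmill exercise would be credited to the open-skill character of table tennis. Advice to older adults on which mode of exercise to choose could then rest on an effect that came from the added drills.

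**Working it through.** No figure in the plan depends on this point, so the check compares the texts and then follows the consequence through the contrasts.

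**Step 1. Cognitive content as described**

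| Element | Open-skill (2.5.1) | Game (2.5.3) | Closed-skill (2.5.2) |
|---|---|---|---|
| Table tennis play | yes | simulated on a phone | no |
| Inhibition drill | yes | none described | none described |
| Task-switching drill | yes | none described | none described |
| Working-memory drill | yes | none described | none described |
| Moderate physical activity | yes | no | yes |

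The drills are listed as part of each session, so they are not incidental. Their duration is not given. With 24 weeks × 3 sessions = 72 sessions, each minute of drills per session is 72 minutes over a fully attended programme.

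**Step 2. What each contrast contains**

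Take assumptions generous to the plan: the game reproduces the cognitive demands of ordinary table tennis, and the ergometer or treadmill reproduces its physical demands. Let P be the physical effect, C the effect of those ordinary cognitive demands, D the drill effect, and I any interplay. Relative to control, open = P + C + D + I, closed = P and game = C.

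- open − game = P + D + I, which the plan would read as physical
- open − closed = C + D + I, which the plan would read as the cognitive part of open-skill play
- open − control = P + C + D + I
- open − closed − game + control = D + I
- closed − control = P and game − control = C, both free of the drills

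Four arms give three independent contrasts for four unknowns, and D and I appear only as a sum. D can be separated only by assuming I = 0, which the plan does not do. Every contrast that uses the open-skill arm includes D.

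**Step 3. Illustration, not an estimate**

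Assume unit SD, two-sided 0.05, and that the drills are the only source of difference between open-skill and game (P = I = 0). With a drill effect of d SD and n per arm, the chance of a significant difference in favour of the open-skill arm is about Φ(d / √(2/n) − 1.96). The n values are 40 (the stated recruitment per arm) and 136/4 = 34.

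| d (assumed) | n = 40 | n = 34 |
|---|---|---|
| 0.2 | 0.14 | 0.13 |
| 0.5 | 0.61 | 0.54 |
| 0.8 | 0.95 | 0.91 |

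For d = 0.5 and n = 40: 0.5 / √(2/40) = 2.236; 2.236 − 1.96 = 0.276; Φ(0.276) = 0.61. The documents do not say where in this range, or outside it, the true drill effect lies.

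**The case against.** Several points can fairly be made for the plan.

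- *The claim is hedged.* The Abstract, the Introduction and part of the Discussion speak only of possible mechanisms that the design may help to show. This is true, but the equivalence statement in the Discussion and the sentence in the Conclusions carry no hedge.
- *The drills are disclosed, and the programme is called specially designed.* This is also true. It makes the description of the arm accurate, but not the statement that the game matches it.
- *The game is said to have multiple modes, and the article is condensed.* A matching task could in principle exist. But both arms are described in some detail, and nothing described for the game corresponds to the three drills.

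A reader might also infer more than the documents support.

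- *That the trial trains participants on its own primary test.* The Introduction says of dual-task research that "concerns exist that the similarity between cognitive assessments and dual-tasks produce a learning effect that impacts the reliability of the results", and it is tempting to turn this against the open-skill arm. But the third drill is a previous-ball colour rule with a stroke as the response, whereas the primary task is to hold and mentally rotate a 4 × 4 matrix. They share a broad construct, not stimuli or operations.
- *That the superimposed benefit mentioned in the Discussion must be proved by an interaction contrast.* The word can simply mean that two benefits add. In that case the interaction contrast would be zero without the drills. With the drills it contains their whole effect, so it could not establish synergy either.
- *That the trial is invalid.* Randomisation still supports comparison of the four programmes as delivered.

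**Conclusion.** The point holds as a contradiction within the plan. The stated equivalence of cognitive content conflicts with the description of the two interventions, and the unhedged mechanism claim in the Conclusions depends on that equivalence. Open-skill versus game does not isolate physical activity, and open-skill versus closed-skill does not isolate open-skill play.

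The direction of concern is that any benefit of the drills would be credited to something else. Its size cannot be given, because neither the drill time nor the drill effect is stated; the illustration rests wholly on assumed effects. The comparisons of closed-skill with control and game with control contain no drill effect. The conclusion relies on section 2.5.3 being a fair description of what the game arm does.

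**What to change.** Reconcile sections 2.5.1, 2.5.3, 3 and 4 in wording:

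1. Delete the statement in the Discussion that the game shares the open-skill arm's cognitive component, and bring the decomposition in the Introduction and section 2.5 into line.
2. In all conclusions, describe the arm as table tennis plus executive-function drills.
3. State that every contrast involving this arm includes the drill effect: against closed-skill, against game, against control, and in any interaction contrast.
4. In the Conclusions, replace the promise to reveal a mechanism with a statement that the trial compares the packages as delivered and cannot attribute a difference to open-skill play or to the physical component alone.

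The interventions, sample size and planned analyses stay as they are. The cost is a narrower mechanism claim, and part of what the article presents as a main strength of the four-group design is given up.
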